### 1.1.2 Type one and Type two errors

Under  $H_0$  we have  $p_1 = p_0$  so that the drift parameter  $\theta$  defined in (1.3) is equal zero. Under  $H_1$  we assume that  $\theta \neq 0$ . The type one error  $\alpha$ , and type two error  $\beta$  of the trial are defined as follows.

$$\begin{aligned}\alpha &= P(Z(1) > z_{1-\alpha} | H_0) = P(N(0, 1) > z_{1-\alpha}) = 1 - \phi(z_{1-\alpha}), \\ \beta &= P(Z(1) \leq z_{1-\alpha} | H_1) = P(N(\theta, 1) \leq z_{1-\alpha}) = \phi(z_{1-\alpha} - \theta),\end{aligned}$$

where  $\phi$  stands for the standard normal distribution. The power of the trial is equal to  $1 - \beta$ .

According to the EAGeR protocol, in order to calculate boundaries for efficacy, we use the two sided alpha spending function as given by

$$\alpha(t) = 2 - 2\phi\left(\frac{z_{1-\alpha/4}}{\sqrt{t}}\right). \quad (1.4)$$

In particular, the total type one error is set to  $\alpha = 0.05$ .

Note that the final value for  $z_{1-\alpha}$  is determined after we calculate boundaries for efficacy using the alpha spending function displayed in (1.4). In order to emphasize this point, in the sequel we denote the final  $z_{1-\alpha}$  by  $z_F$ .

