### G2.2 Intention to treat analysis

The primary analysis of the clinical trial will be “intent to treat” (ITT) analysis based on the total cohort of randomized patients. This approach will be applied to the primary endpoint (live birth) as well as designated secondary endpoints. The difference between the incidence rates of live births for the two treatment groups will be examined by a two-sided test based on the standard Z-score (using the normal approximation to the binomial distribution). The common null hypothesis states that the effect of aspirin on the outcome is null compared to the placebo.

The secondary objectives (as described in Section A) with binary endpoints will be analyzed similarly as comparison of proportions. For binary outcomes such as pregnancy, the time to event may be of interest. In this case, survival analysis methods will be applied with the log-rank test for comparison of the two study treatment groups. For continuous outcome such as birthweight either parametric or non-parametric methods will be used as appropriate. If transformations to approximate a normal distribution are feasible, they will be carried out prior to the parametric analysis. The normality of the data will be examined both graphically using Q-Q plots and by formal tests (Wilks- Shapiro test). For data (either on original or transformed scale) assumed to be normally distributed the comparison of the two treatment groups will be carried out by a t-test. Alternatively if a non-parametric test is required, the Wilcoxon-Mann-Whitney test will be used.

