The following Tables 3 and 4 present results of power calculations for various interim looks plans for the EAGeR trial. These demonstrate the implications of different choices for the number and timing of interim looks. We assume throughout an alpha level of 0.05 and a sample size of 1600 women divided equally to the aspirin and placebo arms of the trial. Previously published studies suggest that for the control group a probability of about 0.70 - 0.80 for live birth given pregnancy ( $P_{preg}$ ) can be expected. Further, the probability of implantation per cycle ( $P_{implant}$ ) was assumed to be constant and in the range between 0.175 and 0.25. Figure 4 shows the probability of live birth (PLB) considering six cycles of menstruation (including both active and passive follow-up):

$$PLB = P_{preg} P_{implant} \sum_{c=1}^6 (1 - P_{implant})^{c-1}$$

**Figure 4.** Probability of live birth versus implantation probability per menstrual cycle

[figure not shown]

Hence a conservative estimate for the live birth rate would be a combination of implantation rate or 17.5% per cycle and a probability of live birth given pregnancy of 70% yielding an estimated value of  $PLB = 0.479$ . The final calculations will be done after the population from which participants are drawn will be identified. A refinement of the calculation can easily incorporate non-fixed probabilities of implantation per cycle

In the following, we consider a range of probabilities for the placebo + folic acid arm of 0.46, 0.48 and 0.50. The effect of the intervention will be measured as the rate ratio (RR) of live birth in the aspirin + folic acid arm compared to placebo + folic acid. We consider effect sizes of 1.15, 1.20 and 1.25. The calculations were preformed using PASS software. Table 3 presents the resulting power for no interim looks and Table 4 shows the power for one or two interim looks for selected outcome probabilities and effect size.

**Table 3.** Power for comparing live birth rates in treatment and placebo groups with no interim looks.

| Live Birth Probability in placebo arm | Live Birth Rate Ratio to be Detected |            |      |
|---------------------------------------|--------------------------------------|------------|------|
|                                       | 1.15                                 | 1.20       | 1.25 |
| 0.46                                  | .77                                  | .96        | .99  |

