## 1.2 Sensitivity analysis

The following calculations are based on one interim look for futility, and no looks for efficacy. Thus we set  $z_F = z_{1-\alpha/2} = 1.96$ .

We first explore a case where we observe no difference between the two arms at time  $t$ . In this case we observe  $\hat{\delta}(t) = 0$ , and the statistic  $Z(t)$  given by (1.1) is equal zero. Thus, the conditional power at time  $t$  is calculated by plugging  $b(t) = 0$  into (1.6). We analyse this case under two extreme scenarios. In the first scenario we let  $p_0 = 0.48$ , and  $RR = 1.2$  so that  $p_1 = 0.576$ ,  $\delta = 0.096$ , and  $\theta = 3.864$ . The power of the trial is 97%, and we get

the following plot.

[figure not shown]

If we decide to stop the trial for futility if the conditional power value is below 30%, then the probabilities for stopping for futility under  $H_0$ ,  $H_1$ , are given by (1.9)-(1.10) and displayed below.

(a)

[figure not shown]

(b)

[figure not shown]

Now suppose that  $p_0 = 0.4$ , and  $RR = 1.15$  so that  $p_1 = 0.46$ ,  $\delta = 0.06$ , and  $\theta = 2.43$ . The power of the trial is then 68%, and the conditional power values at time  $t$  when no

difference is observed between the two arms is displayed in the plot below.

[figure not shown]

If we decide to stop the trial for futility if the conditional power value is below 30%, then the probabilities for stopping for futility under  $H_0$ , and  $H_1$  are displayed below.

(a)

[figure not shown]

(b)

[figure not shown]

We now explore again the case where we observe no difference between the two arms at time  $t$ , for specific values of  $t$ , as a function of  $p_0$ . In the first scenario we let  $t = 0.2$ ,  $p_0 = 0.4, 0.42, 0.44, 0.46, 0.48$ . The treatment proportions will be calculated as  $p_1 = RR * p_0$ , where  $RR = 1.15$ . This yields  $p_1 = 0.46, 0.483, 0.506, 0.529, 0.552$ ,  $\delta = 0.06, 0.063, 0.066, 0.069, 0.072$ , and  $\theta = 2.43, 2.54, 2.65, 2.77, 2.88$ . The power of

the trial is 68%, 72%, 75%, 79%, 82%, with respect to  $p_0$ , and we get the following plot.

[figure not shown]

If we decide to stop the trial for futility if the conditional power value is below 30%, then the probabilities for stopping for futility under  $H_0$ ,  $H_1$ , are given by (1.9)-(1.10) and displayed below.

(a)

[figure not shown]

(b)

[figure not shown]

Now we introduce the same scenario for time  $t = 0.3$ .

[figure not shown]

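### Equation (1.4) of the interim analysis chapter is labelled two-sided with total error 0.05, but it spends only 0.025 by the end of the trial; it is the spend for one tail and should be rewritten or labelled so.

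*Supplement*

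**What the plan says.** The interim analysis chapter, section 1.1.2, introduces equation (1.4) with "in order to calculate boundaries for efficacy, we use the two sided alpha spending function as given by" α(t) = 2 − 2Φ(z_{1−α/4}/√t), and attributes this choice to the protocol. It adds that "the total type one error is set to" α = 0.05, and that the final critical value, called z_F, follows once the efficacy boundaries have been computed from (1.4). Just before, the same section defines α as P(Z(1) > z_{1−α}) under H0 and β with the same quantile.

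Section 1.2 states: "The following calculations are based on one interim look for futility, and no looks for efficacy". It therefore sets z_F = z_{1−α/2} = 1.96. The chapter prints no efficacy boundary derived from (1.4).

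In the protocol, section G2.2 specifies a "two-sided test based on the standard Z-score". Section G.3 says "We assume throughout an alpha level of 0.05 and a sample size of 1600 women divided equally to the aspirin and placebo arms", chooses the O'Brien-Fleming spending function, and gives boundaries in Table 4. For the proposed looks at 0.45 and 0.60 these are ±2.571, ±2.485 and ±2.050.

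**The concern.** A spending function must equal the total type I error at t = 1. One that is called two-sided, with a total of 0.05, should end at 0.05. Equation (1.4) ends at 0.025, and nothing in the chapter says that it applies to each tail separately. The definitions of α and β add a further inconsistency: read literally they describe a one-sided 0.05 rule (1.645), whereas section 1.2 works with 1.96.

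This matters because z_F sets the final test and also enters the conditional power in (1.6). A programmer who took (1.4) as the total two-sided spend would test at two-sided 0.025, below the protocol's level, and would compute lower conditional power from the same data.

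**Working it through.** **Inputs.** N = 1600 with 800 per arm, and α = 0.05 (protocol G.3; chapter 1.1.1 and 1.1.2). Drift θ = δ√N/(2σ), with σ² the mean of p1(1−p1) and p0(1−p0) (chapter equations 1.2 and 1.3). Looks at 0.45 and 0.60 (protocol G.3), treated here as information fractions.

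**1. The chapter's own powers reproduce.** Power = Φ(θ − 1.96).
- p0 = 0.48, RR 1.20: δ = 0.096, θ = 3.864, Φ(1.904) = 0.972; the chapter says 97%.
- RR 1.15, p0 = 0.40 to 0.48: 68.0, 71.8, 75.5, 79.0 and 82.4%; the chapter says 68, 72, 75, 79 and 82%.

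**2. Equation (1.4) at the end of the trial.** z_{0.9875} = 2.2414, so α(1) = 2 − 2Φ(2.2414) = 2 × 0.0125 = 0.0250, half of 0.05.

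**3. Boundaries under the two readings.** These were obtained by numerical recursion on the Brownian-motion scale, with symmetric two-sided boundaries.

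| Looks | (1.4) as total two-sided spend | (1.4) spent in each tail |
|---|---|---|
| none | 2.241 | 1.960 |
| 0.45 | final 2.247 | 3.144, 1.965 |
| 0.60 | final 2.265 | 2.669, 1.981 |
| 0.45 and 0.60 | 3.341, 2.919, 2.265 | 3.144, 2.693, 1.982 |

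Overall type I error is 0.025 under the first reading and 0.050 under the second.

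**4. Overall power with looks at 0.45 and 0.60.**

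| p0, RR | Total spend 0.025 | Total spend 0.05 | Difference, points |
|---|---|---|---|
| 0.48, 1.20 (Table 4 case) | 0.946 | 0.971 | 2.5 |
| 0.48, 1.15 | 0.737 | 0.820 | 8.3 |
| 0.40, 1.15 | 0.569 | 0.676 | 10.7 |
| 0.46, 1.25 | 0.991 | 0.996 | 0.5 |

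A check without looks at p0 = 0.48, RR 1.15 (θ = 2.889): Φ(2.889 − 2.241) = 0.741 against Φ(2.889 − 1.960) = 0.824. Protocol G.3 claims more than 80% power for this scenario, from Table 3.

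**5. Effect on conditional power.** Take a scenario of section 1.2: t = 0.3, p0 = 0.40, RR 1.15, θ = 2.43, no observed difference. Equation (1.6) gives (0.7 × 2.43 − z_F)/√0.7.
- z_F = 1.96: −0.310, conditional power 0.38.
- z_F = 2.241: −0.645, conditional power 0.26.

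These lie on opposite sides of the chapter's illustrative 0.30 threshold.

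**6. Comparison with Table 4.** The first boundary for a look at 0.45 is 2.571 in Table 4, a cumulative spend of 0.0101. Equation (1.4) gives 3.341 as a total or 3.144 per tail. The Table 4 spends (0.0101 at 0.45, 0.0180 at 0.60) agree with 0.05t², that is 0.05 × 0.2025 and 0.05 × 0.36.

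**The case against.** The strongest reply is that (1.4) is correct and only badly labelled. The quantile z_{1−α/4} arises when α has already been halved for two tails: 2 − 2Φ(z_{1−α/4}/√t) is exactly the O'Brien-Fleming-type function for one tail at 0.025. On this view the word two-sided describes the boundaries, and 0.05 is the sum over both tails. The only z_F that the chapter uses supports this: with no efficacy look the per-tail reading gives exactly 1.96, whereas the literal reading would give 2.241, which is printed nowhere. Likewise, 1.645 is never used; z_{1−α} serves as a placeholder that is later renamed z_F.

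Most of this stands. A reader might infer that the trial's final critical value is in fact about 2.25, that about 8 points of power have been lost, or that the chapter's powers and plots are wrong. The documents do not support any of these: the printed powers all reproduce at 1.96, and the sensitivity analysis already corresponds to a two-sided 5% test.

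What does not stand is that the text settles the matter. The chapter never says per tail; it calls the function two-sided and speaks of a total. Its equation and its stated error level disagree on the page, and no printed efficacy boundary shows which was meant. Table 4 cannot decide it, since it matches neither reading.

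**Conclusion.** Equation (1.4) is wrong as written and labelled: it reaches 0.025, not the stated total of 0.05. The per-tail reading is the likelier intention, and under it the total is 0.05, z_F is 1.96 to 1.98, and no power is lost.

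The harm is therefore conditional on coding (1.4) as the total two-sided spend. In that event the final critical value is 2.24 to 2.27. The loss depends on the scenario: about 2.5 points in the Table 4 design case, about 8 at p0 = 0.48, RR 1.15 (enough to fall below the protocol's 80%), and about 11 at p0 = 0.40, RR 1.15. An 8-point figure should not be quoted without its scenario. The direction is conservative, so type I error is not inflated.

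The boundary and power figures assume equal arms and information fractions of 0.45 and 0.60. In protocol G.3 those fractions are of elapsed time, while the chapter defines t as n/N, so the actual fractions may differ.

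**What to change.** - Write (1.4) as α(t) = 4 − 4Φ(z_{1−α/4}/√t), so that α(1) = 0.05. Alternatively keep it and state that it is spent in each tail, α/2 per side.
- Replace z_{1−α} by z_{1−α/2} in the definitions of α and β, and write the type I error as P(|Z(1)| > z_{1−α/2}) so that the definition is two-sided.
- Print the efficacy boundaries and z_F for the planned looks: ±3.144, ±2.693 and ±1.982 if the information fractions are 0.45 and 0.60. State that this z_F enters (1.6) when efficacy looks are made.
- Reconcile these with protocol Table 4 (±2.571, ±2.485, ±2.050). Printing 1.982 alone would leave two different final boundaries in the documents.

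The cost is one equation or one sentence, two definitions, a short boundary table and a reconciling statement. The section 1.2 powers and plots need no rerun, because they already use 1.96 with no efficacy look.

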### 1.1.3 Stopping for futility

#### The conditional power

Denote the Brownian motion value at time  $t$  by  $B(t)$ . Then we have that  $B(t) = \sqrt{t}Z(t)$ , where  $Z(t)$  is given by (1.1). Given that we observe at time  $t$  the value  $B(t) = b(t)$ , the conditional power at time  $t$  is define by

$$CP(t, \theta) = P(B(1) > z_F | B(t) = b(t)).$$

Using the Brownian motion framework for our calculations, this probability is equal to

$$\phi(Z_{CP}(t, \theta)), \quad (1.5)$$

where

$$Z_{CP}(t, \theta) = \frac{b(t) + (1-t)\theta - z_F}{\sqrt{1-t}}. \quad (1.6)$$

## Remarks.

- (1) At the beginnig of the trial  $t = 0$ , and  $b(0) = 0$ . Thus, we have

$$CP(0, \theta) = \phi(\theta - z_F) = 1 - \beta,$$

the power of the trial.

- (2) The drift parameter  $\theta$  in (1.6) resembles the effect size from time  $t$  until the end of the trial.
- (3) Except for  $t$ , and  $\theta$ , the conditional power value is dependent on  $z_F$ .

Remark (2) implies that there are other options for calculating the conditional power value. For example, one can assume that the effect size from now on is zero, which results in a different value  $CP(t, \theta = 0)$ . Also, we can replace the drift parameter  $\theta$  in (1.6), by its estimator  $\hat{\theta} := b(t)/t$  (current trend), which will give us another conditional power value. In what follows, we focus on the conditional power value as given by (1.6).

## Probability for stopping for futility

Let us look again at the expression for  $Z_{CP}(t, \theta)$  as given by (1.6). If we consider this term before we observe  $B(t) = b(t)$ , then  $Z_{CP}(t, \theta)$  is a random variable, since  $B(t) \sim N(t\theta, t)$ . In particular, in this case we have

$$Z_{CP}(t, \theta) = \frac{B(t) + (1-t)\theta - z_F}{\sqrt{1-t}} \sim N\left(\frac{t\theta + (1-t)\theta - z_F}{\sqrt{1-t}}, \frac{t}{1-t}\right). \quad (1.7)$$

Based on the expression above we can calculate the probability of stopping for futility. Suppose that we decide to stop for futility if the conditional power value as given by (1.5) is less than some pre-specified value  $\gamma$ , say 0.3; i.e., we will stop the trial for futility, if at time  $t$  we have  $CP(t, \theta) = P(B(1) > z_F | B(t) = b(t)) \leq 0.3$ . Using (1.7) we can calculate the probability for such an event. Specifically, this probability is given by

$$P_{stop} = P(CP(t, \theta) \leq \gamma) = P(Z_{CP}(t, \theta) \leq z_\gamma). \quad (1.8)$$

According to (1.8), we can specify a boundary value for the Brownian motion for which we will stop the trial for futility. This boundary value is given by

$$b_\gamma(t) := z_\gamma \sqrt{1-t} - (1-t)\theta + z_F.$$

Thus, we will stop the trial for futility if  $B(t) \leq b_\gamma(t)$ . The probability for stopping for futility then takes the form

$$P_{stop} = P(B(t) \leq b_\gamma(t)).$$

Note that here we can compute the stopping probability under the assumption that  $B(t) \sim N(0, t)$ , which we denote by  $P_{stop}(H_0)$ . Similarly, we can compute the stopping probability

under the assumption that  $B(t) \sim N(t\theta, t)$ , which we denote by  $P_{stop}(H_1)$ . We obtain the following expressions for the probability for stopping for futility.

$$P_{stop}(H_0) = \phi\left(\frac{b_\gamma(t)}{\sqrt{t}}\right), \quad (1.9)$$

$$P_{stop}(H_1) = \phi\left(\frac{b_\gamma(t) - t\theta}{\sqrt{t}}\right). \quad (1.10)$$

### Remarks.

- (1) Smaller  $B(t)$  values are required to yield low CP values under  $H_1$  than under the current trend or  $H_0$ .
- (2) Here too, there are other options for calculating the probability for stopping for futility with respect to what we plug in for the drift parameter  $\theta$ , and in addition, to the expectation of the random variable  $B(t)$ .

When we stop a trial for futility, we expose ourselves to a type two error. For example, when we have only one interim look for futility stopping (and no other looks for efficacy), the total errors  $\beta_T$  and  $\alpha_T$  of the trial are then calculated by

$$\begin{aligned} \beta_T &= P_{H_1}(B(t) \leq b_\gamma(t)) + P_{H_1}(\{B(t) > b_\gamma(t)\} \cap \{B(1) \leq z_F\}), \\ \alpha_T &= P_{H_0}(\{B(t) > b_\gamma(t)\} \cap \{B(1) > z_F\}). \end{aligned}$$

Note that  $\alpha_T$  is smaller than the original type one error  $\alpha$ . If other interim looks are planned for efficacy, then the calculation will be in the same spirit, but different.

## 1.2 Sensitivity analysis

The following calculations are based on one interim look for futility, and no looks for efficacy. Thus we set  $z_F = z_{1-\alpha/2} = 1.96$ .

We first explore a case where we observe no difference between the two arms at time  $t$ . In this case we observe  $\hat{\delta}(t) = 0$ , and the statistic  $Z(t)$  given by (1.1) is equal zero. Thus, the conditional power at time  $t$  is calculated by plugging  $b(t) = 0$  into (1.6). We analyse this case under two extreme scenarios. In the first scenario we let  $p_0 = 0.48$ , and  $RR = 1.2$  so that  $p_1 = 0.576$ ,  $\delta = 0.096$ , and  $\theta = 3.864$ . The power of the trial is 97%, and we get

the following plot.

[figure not shown]

If we decide to stop the trial for futility if the conditional power value is below 30%, then the probabilities for stopping for futility under  $H_0$ ,  $H_1$ , are given by (1.9)-(1.10) and displayed below.

(a)

[figure not shown]

(b)

[figure not shown]

Now suppose that  $p_0 = 0.4$ , and  $RR = 1.15$  so that  $p_1 = 0.46$ ,  $\delta = 0.06$ , and  $\theta = 2.43$ . The power of the trial is then 68%, and the conditional power values at time  $t$  when no

difference is observed between the two arms is displayed in the plot below.

[figure not shown]

If we decide to stop the trial for futility if the conditional power value is below 30%, then the probabilities for stopping for futility under  $H_0$ , and  $H_1$  are displayed below.

(a)

[figure not shown]

(b)

[figure not shown]

We now explore again the case where we observe no difference between the two arms at time  $t$ , for specific values of  $t$ , as a function of  $p_0$ . In the first scenario we let  $t = 0.2$ ,  $p_0 = 0.4, 0.42, 0.44, 0.46, 0.48$ . The treatment proportions will be calculated as  $p_1 = RR * p_0$ , where  $RR = 1.15$ . This yields  $p_1 = 0.46, 0.483, 0.506, 0.529, 0.552$ ,  $\delta = 0.06, 0.063, 0.066, 0.069, 0.072$ , and  $\theta = 2.43, 2.54, 2.65, 2.77, 2.88$ . The power of

the trial is 68%, 72%, 75%, 79%, 82%, with respect to  $p_0$ , and we get the following plot.

[figure not shown]

If we decide to stop the trial for futility if the conditional power value is below 30%, then the probabilities for stopping for futility under  $H_0$ ,  $H_1$ , are given by (1.9)-(1.10) and displayed below.

(a)

[figure not shown]

(b)

[figure not shown]

Now we introduce the same scenario for time  $t = 0.3$ .

[figure not shown]

If we decide to stop the trial for futility if the conditional power value is below 30%, then the probabilities for stopping for futility under  $H_0$ ,  $H_1$ , are given by (1.9)-(1.10) and displayed below.

(a)

[figure not shown]

(b)

[figure not shown]

Supplement: S2 File — (PDF) [file pone.0200533.s003.pdf]
